[figure not shown]

### List of Abbreviations

| Abbreviation        |                                    | Abbreviation |                 |
|---------------------|------------------------------------|--------------|-----------------|
|  C-MTG |  C Mixed Triglyceride | FE1          | Faecal Elastase |
| PDAC                | Pancreatic adenocarcinoma          |              |                 |

# 1 Introduction

## 1.1 Purpose of SAP

This statistical analysis plan (SAP) describes in detail the methods that will be used to analyse the data collected as part of the DEPEND study. This will form the basis of the final publication. The final analysis will follow the SAP to ensure that the analyses are conducted in a scientifically valid manner and to avoid post hoc decisions which may affect the interpretation of the statistical analysis. Any deviations from the SAP will be detailed in the final report.

## 1.3 Study background and rationale (short synopsis)

The incidence of all types of pancreatic cancer in the UK is 9.6 per 100,000. Pancreatic adenocarcinoma (PDAC) is the most common subtype making up 85% of cases. It is regarded as the most lethal of all the common cancers on account of its insidious nature, often only presenting when causing compression of the distal biliary tree resulting in jaundice; by which point it has usually extended beyond a resectable margin and/or metastasised. This is the case in 79% of pancreatic cancer diagnoses, resulting in a 5-year survival rate of less than 5%; something which hasn't improved in 40 years. Recent studies have shown that around 40% of patients diagnosed with PC require three or more visits to their general practitioner (GP) before they are referred to a specialist thereby leading to a delay in the diagnosis of PC. A recent survey of GPs, showed that not having access to a reliable diagnostic referral pathway is a major barrier to the early diagnosis of PC.

We propose using alternative tests to determine if they are suitable for detecting PDAC in certain populations. This involves the use of a  $^{13}\text{C}$ -mixed-triglyceride breath test to test for pancreatic enzyme function and to identify potential lesions which may affect the inner workings of the pancreas. Lipase is an enzyme secreted by the pancreas used in the digestion of fats, and may provide a suitable target for investigating pancreatic function as failure to adequately digest fat could suggest possible duct obstruction or reduced secretory capability due to the presence of a tumour. In addition to this test, faecal elastase can detect patients with insufficient pancreatic function through a single stool sample, as a lower value is associated with poor pancreatic function.

## 1.4 Objectives

- 1) Can the  $^{13}\text{C}$ -mixed triglyceride breath test and the measurement of faecal elastase-1 be used to distinguish between patients with PDAC and healthy volunteers?
- 2) Do the 1, 2, and 3-hour  $^{13}\text{C}$ -mixed triglyceride breath tests perform similarly in their ability to classify PDAC patients in comparison to the 4-hour test?

## **1.5 Definition of primary endpoint**

### **1.5.1 Pancreatic adenocarcinoma diagnosis**

The primary endpoint for this study is a prediction for stage I or II pancreatic adenocarcinoma (PDAC) vs a prediction of no PDAC.

## **1.6 Analysis principles**

All analyses will be reported according to the TRIPOD Statement

## **1.7 Description of study design**

DEPEND is a case-control prognostic study. Participants with known PDAC will be recruited alongside healthy controls, and a subset of participants with chronic pancreatitis.

## **1.8 Power and sample size**

The sample size calculation was based on a previous study assessing pancreatic exocrine function using a  $^{13}\text{C}$ -MTG breath test in healthy subjects and patients with a localised pancreatic mass (Kato *et al*, 1993). Using data from this study, we calculated that a sample size of 25 subjects in each group will give 100% power to detect a difference of 17.8% in the  $^{13}\text{C}$ -MTG breath test between patients with PC and healthy subjects assuming a standard deviation of 10.5% in patients with PC at a significance level of 5% using two tailed test. The power calculation was carried out using a statistical software (IBM SPSS Sample Power version 3).

## **1.9 Randomisation details**

DEPEND is a non-randomised study.

## **1.10 Timing of planned analyses**

### **1.10.1 Interim analyses and early stopping**

There are no planned interim analyses or early stopping rules for this study.

### **1.10.2 Final analysis**

The final analysis will be carried out once all participants have had their study visit and the results of their faecal elastase results have been returned.

## **2 Statistical considerations**

### **2.1 Definition of analysis populations**

#### **2.1.1 PDAC population**

The PDAC population will consist of 25 participants with a known diagnosis of PDAC.

#### **2.1.2 Healthy control population**

The healthy control population will consist of 25 participants with no known diagnosis of PDAC. This population will be age- and sex- matched to those in the PDAC population.

#### **2.1.3 Chronic pancreatitis population**

The chronic pancreatitis population will consist of up to 10 participants with a known diagnosis of chronic pancreatitis but no known diagnosis of PDAC.

### **2.2 Analysis software**

The analysis will be conducted using Stata v16 or SAS v9.3, or higher.

### **2.3 Methods for handling data**

#### **2.3.1 Withdrawal from trial**

All data up until the point of patient withdrawal from the trial will be used in analyses unless the patient withdrew consent and does not wish for the data already collected prior to withdrawal to be used for the trial.

#### **2.3.2 Missing data**

Multiple imputation will be used for key variables with missing data.

#### **2.3.3 Outliers**

Patients undergoing the  $^{13}\text{C}$ -mixed triglyceride breath test are recommended to remain seated for duration of the test, because physical activity will affect the excretion rate (Kalivianakis *et al*, 1997). Adherence to the protocol will be measured, and additional analyses will be conducted to assess model performance in those who remained seated, and comparing excretion values in compliant and non-compliant participants.

#### **2.3.4 Assumption checking and alternative methods**

There are no planned assumption checks in this analysis.

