#### **2.5.1 Model building**

Logistic regression models will be constructed predicting PDAC status using  $^{13}\text{C}$ -mixed triglyceride breath test and faecal elastase values as described in section 2.4. Multivariable logistic regression models will then be constructed with the aim of finding the best-fitting combination of cut-offs for the  $^{13}\text{C}$  and faecal elastase values.

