#### **3.3 Primary endpoint**

##### **3.3.1 Pancreatic cancer diagnosis**

The primary endpoint for this study is the prediction of PDAC. PDAC status is known at recruitment (i.e. all participants in the PDAC cohort are positive, all others are negative). Several logistic multivariable models will be constructed using results from the C-mixed triglyceride breath test and fecal elastase tests, with appropriate data transformations as outlined in section 2.4. All final regression model results will be reported. Models will be validated and adjusted for optimism using bootstrapping techniques (Steyerberg *et al*, 2001). Performance measures include sensitivity, specificity, positive predictive value, and negative predictive value. In order to evaluate these, numerous cut-offs for defining predicted cancer positivity in the underlying risk score will be evaluated with the study team. Discrimination will be measured using the R2 and D statistic. Calibration will be assessed visually with the aid of calibration plots, comparing observed and predicted risks in each tenth of predicted risk.

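### Logistic models on binary cut-offs with 25 cases and 25 to 35 negatives carry a real risk of separation, and SAP section 2.3.4 plans no check and names no alternative method

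*SAP*

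**What the plan says.** - Model: "Logistic regression models will be constructed predicting PDAC status using" the breath test and faecal elastase (SAP 2.5.1). Multivariable models then look for the combination of cut-offs that fits best. No estimator is named.
- Predictors (SAP 2.4.1 and 2.4.2): fixed breath-test cut-offs at 1, 2, 3 and 4 hours, cut-offs at the healthy-control mean, Youden cut-offs, and faecal elastase below 200 or below 100 µg/g. Faecal elastase also enters as a continuous value.
- Cases: "The PDAC population will consist of 25 participants with a known diagnosis of PDAC" (SAP 2.1.1).
- Healthy controls: "The healthy control population will consist of 25 participants with no known diagnosis of PDAC" (SAP 2.1.2).
- Chronic pancreatitis: "The chronic pancreatitis population will consist of up to 10 participants with a known diagnosis of chronic pancreatitis" (SAP 2.1.3).
- Outcome coding: "all participants in the PDAC cohort are positive, all others are negative" (SAP 3.3.1). Objective 1 (SAP 1.4), by contrast, is PDAC against healthy volunteers.
- Validation: "Models will be validated and adjusted for optimism using bootstrapping techniques" (SAP 3.3.1).
- Checks and alternatives: "There are no planned assumption checks in this analysis" (SAP 2.3.4). This is the section's only sentence. Its heading also covers alternative methods, but none is given there or elsewhere.
- Software: "The analysis will be conducted using Stata v16 or SAS v9.3, or higher" (SAP 2.2).

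**The concern.** A binary predictor has a finite maximum-likelihood odds ratio only if all four cells of its table against the outcome are occupied. With 25 per group, two kinds of planned cut-off can leave one empty. A cut-off that few healthy people fall below may have no positive control. A cut-off at the healthy-control mean may have every case below it. Bootstrap refits add to the risk, because a resample can lose the one or two participants who kept the estimate finite.

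The SAP promises to report all final regression results, to give 95% confidence intervals throughout and to correct for optimism. With an empty cell, the printed odds ratio and its Wald interval depend on where the algorithm stops. If the software instead removes the participants it predicts perfectly, or failed resamples are discarded, the performance and optimism estimates change too. Choosing a rescue after seeing a failed fit is the kind of post hoc decision that SAP 1.1 sets out to avoid.

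**Working it through.** **Inputs from the SAP.** 25 cases, 25 healthy controls, 0 to 10 chronic pancreatitis participants (2.1); difference 17.8, SD 10.5, two-sided 5% (1.8).

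**Assumptions not in the SAP.** Normal data; SD 10.5 in both groups (the SAP gives it for patients only); cut-off specificity of 90% to 97.5%; the share of chronic pancreatitis participants below a cut-off. In the simulations, faecal elastase is shifted by 0.8 or 1.7 SD, its correlation with the breath test is 0.5, and chronic pancreatitis values are as low as PDAC values.

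**1. The plan's own figure.** 17.8 / (10.5 × √(2/25)) = 5.99. Power ≈ Φ(5.99 − 1.96) = 99.997%, so the stated 100% reproduces. The shift is 17.8/10.5 = 1.70 SD.

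**2. One cut-off, 25 v 25.** With sensitivity s and specificity c, the chance of no finite estimate is

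1 − [1 − s^25 − (1−s)^25] × [1 − c^25 − (1−c)^25].

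At high specificity and moderate sensitivity this is nearly c^25:

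| Specificity | Sensitivity implied by 1.70 SD | No finite estimate |
|---|---|---|
| 90% | 66% | 0.90^25 = 7% |
| 95% | 52% | 0.95^25 = 28% |
| 97.5% | 40% | 0.975^25 = 53% |

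A cut-off midway between the group means gives 0.8%.

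**3. Control-mean cut-off.** Sensitivity is Φ(1.695) = 95.5%, so all 25 cases fall below it with probability 0.955^25 = 32%. Simulation with the mean estimated from the same controls gives 32% to 33% for 25 v 25 and 31% to 34% with ten chronic pancreatitis negatives. The empty cell is among the cases, so extra negatives do not help.

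**4. Chronic pancreatitis as negatives, one fixed cut-off.** If 20% of ten such participants fall below the cut-off, multiply by 0.8^10 = 0.107: 0.277 × 0.107 = 3% and 0.531 × 0.107 = 6%. If 50% do, the result is below 0.1%. With only five participants, 0.8^5 = 0.328 gives 9% and 17%.

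**5. Other predictors (1,500 simulated data sets per scenario).**

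| Predictors | 25 v 25 | With ten chronic pancreatitis negatives |
|---|---|---|
| Youden cut-off | about 10% | 5% to 6% |
| Two cut-offs, 95% specificity | 44% to 49% | 0.3% to 3% |
| Two cut-offs, 97.5% specificity | 73% to 77% | 1% to 9% |
| Continuous only | 0% to 0.1% | 0% |

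**6. Bootstrap.** With k positive controls among 50 participants, a resample has none with probability (1 − k/50)^50: 36% for k = 1 and 13% for k = 2. At 95% specificity, 25 v 25, simulation gives 43% to 44% of resamples without a finite estimate on average, and about 23% when the original fit is finite. With ten chronic pancreatitis negatives the average is about 1%.

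**7. What a separated fit prints.** Take 15/25 cases and 0/25 controls below a cut-off:

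| Fit | Log odds ratio | SE |
|---|---|---|
| Maximum likelihood, 8 iterations | 10.5 | 19 |
| 15 iterations | 17.5 | 620 |
| 25 iterations | 23.5 | 12,444 |
| Firth | 4.32 | 1.53 |

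For this one table, Firth equals adding one half to each cell: ln[(15.5/10.5)/(0.5/25.5)] = 4.32.

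**The case against.** The strongest reply is that the high figures belong to the wrong contrast. SAP 3.3.1 counts chronic pancreatitis participants as negatives, and many may fall below an insufficiency cut-off. This stands for the fixed cut-offs: with ten such participants the risk is low. It does not dispose of the point. The SAP allows up to ten, so there may be fewer; Objective 1 concerns healthy volunteers; and the control-mean cut-off is unaffected.

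Second, the SAP states no specificity for any cut-off. That stands, so the frequency is a range under assumptions.

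Third, a reader might infer that risk scores become arbitrary. They do not if everyone is retained. With 13/25 cases and 0/25 controls positive, fitted risks settle at 1.000 and 12/37 = 0.324, and the log-likelihood at 12 ln(12/37) + 25 ln(25/37) = −23.313. Risk ranking, apparent sensitivity and specificity, and comparisons of fit by likelihood survive.

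Fourth, section 2.3.4 says that no checks are planned, which is not a ban. Empty cells would also show in the cohort summaries of breath-test cut-offs in SAP 3.4. That is fair, but seeing an empty cell does not settle how the model is then fitted. Nor does the SAP say that failed resamples will be discarded; it leaves this open.

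**Conclusion.** The gap is real and worth closing before analysis. Several planned cut-off models can fail to give a finite odds ratio, and the section that should name a fallback names none. The control-mean cut-off is the firmest case: about one study in three in either contrast, given normality and equal SDs. For fixed cut-offs the size depends on the contrast and on unknown specificity: about 7% to 53% against healthy controls, but about 3% to 6% or less with ten chronic pancreatitis negatives of whom at least 20% are below the cut-off (specificity 95% to 97.5%). Youden cut-offs run at about 5% to 10%.

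A reader might infer that the planned logistic analysis as a whole will often fail. The document does not support that: continuous predictors are essentially unaffected, and so are cut-offs near the midpoint between the groups. The certain damage under maximum likelihood is to the odds ratio and its Wald interval. Damage to performance and optimism estimates follows only if participants or resamples are dropped.

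**What to change.** State in SAP 2.3.4 that:

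- logistic models containing cut-off predictors, and all their bootstrap refits, will be fitted by Firth penalised likelihood with profile-likelihood 95% confidence intervals;
- predicted risks and calibration plots from these models will use an intercept correction, because the Firth penalty shifts the average predicted risk;
- no participant, predictor or resample will be dropped for perfect prediction;
- the number of separated fits, in the original data and among the resamples, will be reported.

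Models with continuous predictors only may stay as planned unless separation occurs. The same rule should cover the analysis restricted to participants who stayed seated (SAP 2.3.3), where numbers may be smaller.

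The cost is a paragraph of SAP text, a standard option or add-on in the named software, a little extra programming and slight shrinkage of the coefficients. Sample size and data collection do not change.

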#### **2.3.5 Data transformations**

Data transformations are outlined in section 2.4.

### **2.4 Definition of key derived variables**

#### **2.4.1 The cumulative % $^{13}\text{C}$ -dose recovered (cPDR) during exhalation over the study period**

After an overnight fast for 12hrs, each participant will be asked to provide 2 baseline breath samples by blowing into  $2 \times 10\text{ml}$  exetainer tubes through a straw while wearing a facemask before they are given orally 250mg of 2- $^{13}\text{C}$ -octanoyl-1,3-distearin ( $^{13}\text{C}$ -MTG -Cambridge Isotope Laboratories, Andover, MA,

USA) together with a solid test meal consisting of 12g of butter on top of a single crispbake and 200ml water. After the test meal is given to each participant, post-prandial breath samples will be then collected every 30mins for 4 hours. After providing breath samples for 4 hours, participants will then be provided with a light meal and then asked to go home. The collected breath samples from the  $^{13}\text{C}$ -MTG breath test will be then analysed for the ratio of  $^{13}\text{CO}_2$  to  $^{12}\text{CO}_2$  by [name] using a Continuous Flow Isotope Ratio Mass Spectrometer (CF-IRMS SERCON Ltd, Crewe, UK) at the Southampton Centre for Biomedical Research Mass Spectrometry (SCBR mass spectrometry). The increase in  $^{13}\text{CO}_2$  content with regard to the baseline value of the initial breath sample is expressed as atom % excess and we will express the results of the  $^{13}\text{C}$ -MTG breath test as the cumulative percentage of  $^{13}\text{C}$ -label recovered on breath every 30 minutes until the 4 hour time point (240 minutes).

Normal values for  $^{13}\text{C}$  exhalation have been defined in healthy volunteers previously (Keller *et al*, 2014). Participants will be classified as exhibiting pancreatic exocrine insufficiency (PEI) if their cumulative  $^{13}\text{C}$  exhalation is below 1.6%, 4.2%, 7.9% or 13.8% at the 1, 2, 3 and 4-hour time points respectively. We will also consider defining cut-offs for PEI based on the mean values for the healthy controls at the respective time points, and the intervening 30-minute time points. We will also examine which cut-off for PEI best discriminates between PDAC and other participants at each time point in this study using the Youden index.

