#### **3.4 Secondary endpoints**

The distribution of C cumulative exhalation will be summarised at 1, 2, 3 and 4-hours, by cohort.

The proportion of participants with C cumulative exhalation below cut-offs outlined in section 2.4.1 will be summarised by cohort.

The proportion of participants whom remain seated during the 4-hour C-mixed triglyceride breath test will be summarised by cohort.

The distribution of the faecal elastase test will be summarised by cohort, including the proportion of participants who returned a sample and whether the sample was collected at the visit or post-visit.

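### SAP 2.4.1 calls a threshold tuned to PDAC status a PEI cut-off, and 3.4 as worded tabulates the proportion below it by cohort, so the PDAC-versus-others contrast in those rows is optimistic and uncorrected

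*SAP*

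**What the plan says.** SAP section 2.4.1 describes three kinds of breath-test cut-off, and calls all of them cut-offs for PEI.

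- **Published limits.** Participants are to be classified as having PEI if cumulative exhalation is below 1.6%, 4.2%, 7.9% or 13.8% at 1, 2, 3 and 4 hours.
- **Healthy-control means** from this study, which the SAP will consider.
- **A Youden-index value**: "We will also examine which cut-off for PEI best discriminates between PDAC and other participants at each time point in this study".

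Section 3.4 then lists, as a secondary endpoint, that the proportion of participants with "cumulative exhalation below cut-offs outlined in section 2.4.1 will be summarised by cohort". It does not say which of the three kinds it means.

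Section 3.3.1 plans bootstrap validation and optimism adjustment for the regression models. No such adjustment is stated for the proportions in 3.4.

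On cohort sizes, "The PDAC population will consist of 25 participants with a known diagnosis of PDAC" and "The healthy control population will consist of 25 participants with no known diagnosis of PDAC". In addition, "The chronic pancreatitis population will consist of up to 10 participants with a known diagnosis of chronic pancreatitis". The other participants in the Youden comparison therefore number up to 35.

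**The concern.** There are two problems, one of meaning and one of bias.

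**Meaning.** PEI is a state of pancreatic function. The Youden value is chosen to separate PDAC from everyone else, and everyone else includes participants with chronic pancreatitis, who may have PEI themselves. The criterion counts each of them who falls below the cut-off as an error. What it yields is a decision threshold for PDAC, not a limit of normal pancreatic function.

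**Bias.** Cohort membership picks the threshold, and the table then compares the proportion below it across the same membership in the same people. The gap between PDAC and others at that threshold is the largest the sample allows at that time point, so on average it exceeds the gap that the same threshold would show in new participants.

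At stake is a secondary summary. A reader shown several sets of proportions, all under cut-offs named for PEI, could not tell that one set was tuned to the cohort label. That set could be taken as evidence on how much more common PEI is in PDAC. Neither the primary models nor the sample size is affected.

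**Working it through.** **Inputs from the SAP**

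- Section 1.8: "a sample size of 25 subjects in each group will give 100% power to detect a difference of 17.8" per cent, "assuming a standard deviation of 10.5% in patients with PC", "at a significance level of 5% using two tailed test".
- Sections 2.1.1 to 2.1.3: 25 PDAC, 25 healthy, up to 10 chronic pancreatitis, so 25 against 25 + 10 = 35.

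**Assumptions not in the SAP**

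- Cumulative exhalation is normal, with SD 10.5 in every cohort (the SAP gives it only for PDAC patients).
- The chronic pancreatitis mean is unknown, so it is set once at the healthy mean and once at the PDAC mean.

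**Step 1: the plan's own figure.** The standardised difference is 17.8 / 10.5 = 1.695. Power is approximately Φ(1.695 × √(25/2) − 1.960) = Φ(5.994 − 1.960) = Φ(4.034) = 0.99997. A noncentral-t calculation with 48 degrees of freedom gives 0.99995. Both round to the stated 100%. That figure is not in dispute; it shows that the inputs are read as intended.

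**Step 2: optimism of the Youden rows.** For a cut-off c, J(c) = (proportion of PDAC below c) − (proportion of others below c). In each of 5,000 simulated studies per scenario, c was chosen to maximise J in the sample. The apparent proportions below c were then compared with the true population proportions below the same c:

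- true PDAC proportion = Φ((c − PDAC mean) / 10.5);
- true proportion in others = [25 Φ((c − healthy mean) / 10.5) + 10 Φ((c − chronic pancreatitis mean) / 10.5)] / 35.

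Optimism is the mean apparent value minus the mean true value. Last digits may differ by 0.1 through rounding.

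| True difference, healthy minus PDAC | Chronic pancreatitis mean | PDAC below c: apparent / true | Excess | Gap J: apparent / true | Excess |
|---|---|---|---|---|---|
| 0 | same as all | 57.4% / 48.5% | 8.9 | 15.0 / 0.0 | 15.0 |
| 10.5 | as healthy | 73.9% / 67.3% | 6.6 | 47.1 / 35.7 | 11.4 |
| 10.5 | as PDAC | 73.4% / 65.9% | 7.4 | 37.5 / 24.7 | 12.7 |
| 17.8 | as healthy | 84.1% / 78.6% | 5.4 | 67.2 / 57.9 | 9.3 |
| 17.8 | as PDAC | 83.0% / 76.7% | 6.3 | 51.0 / 40.4 | 10.6 |

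A repeat with 10,000 studies per scenario and a different random seed agreed within 0.3 points for every excess.

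**Step 3: what is not affected.** A cut-off fixed before the data, such as the published 13.8% at 4 hours, involves no selection, so its optimism is zero.

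**Step 4: contrast versus PDAC proportion.** The Youden index maximises the gap, not the PDAC proportion. With no true difference, the 5th to 95th percentile range of the apparent PDAC proportion is 8% to 100%. At the planning difference, a cut-off at the healthy mean would put Φ(17.8 / 10.5) = Φ(1.695) = 95% of PDAC below it, more than the 84% under Youden. It would also put about half of the healthy controls below it.

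**The case against.** The case for leaving the text alone has some force.

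- **Section 3.4 does not use the term PEI or name the Youden value.** The operative rule in 2.4.1 is the published one. The Youden step is only something to be examined, and the preceding sentence of 3.4 names the same 1, 2, 3 and 4 hours as the published limits. A reading confined to the published limits is possible. This stands in part: the Youden value enters 3.4 only through an open cross-reference. But the wording excludes nothing, and section 1.1 says the SAP is meant to prevent post hoc decisions.
- **The Youden sentence may mean comparing the cut-offs already listed.** That reading is possible, but the text does not limit the search to them. Choosing among candidates by PDAC status in the same data would still be a selection, though probably with less optimism than a free search.
- **The proportions below a Youden cut-off are simply apparent sensitivity and one minus specificity.** That is correct, and it is why they belong with the accuracy results rather than in a by-cohort summary of cut-offs named for PEI.

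Three stronger readings are tempting, and the SAP does not support them.

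- A reader might infer that the PEI frequency reported for PDAC is inflated by construction throughout. It is not: the published-limit rows are unaffected, no objective or endpoint is defined as PEI frequency, and the Youden rows inflate the PDAC proportion only on average.
- A reader might add a further penalty for picking the best time point. Section 2.4.1 works at each time point, and 3.4 picks none.
- A reader might take the difference between the proportions below a Youden value and below 13.8% as bias. Two different thresholds give different proportions in any case; only the excess over the true proportion at the same threshold is bias.

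**Conclusion.** The point holds for the Youden-based rows only. A threshold selected on PDAC status is misnamed as a PEI cut-off, the unrestricted reference in 3.4 brings it into a by-cohort summary, and the stated optimism adjustment does not reach that summary.

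The PDAC-versus-others gap in those rows is overstated by about 15 points if there is no true difference and by about 9 to 11 points at the planning difference. The PDAC proportion is overstated on average by about 9 points and by about 5 to 6 points respectively. These sizes rest on normality, a common SD of 10.5, 25 against 35 participants, and the two placements of the chronic pancreatitis mean. They are averages over studies, not a prediction for this one.

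This is a worthwhile correction to a secondary summary. It does not threaten the primary analysis.

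**What to change.** 1. In 2.4.1, call the Youden value a PDAC classification threshold and stop describing it as a cut-off for PEI.
2. In 3.4, limit the breath-test proportions by cohort to cut-offs set without PDAC status, and name them: 1.6%, 4.2%, 7.9% and 13.8% at 1, 2, 3 and 4 hours.
3. In 3.3.1, report the Youden thresholds as sensitivity and specificity for PDAC, with optimism adjustment in which the threshold is selected afresh within each bootstrap sample.

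No new data are needed, and the Youden analysis is kept. The cost is a few lines of SAP wording, slightly more programming for the bootstrap, and somewhat less favourable accuracy figures.
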